## Abstract

**Introduction:**

Anticoagulants are arguably the most important drug family of all, based on the frequency and duration of their use, and the clinical importance and frequency of benefits and harms. Several direct acting oral anticoagulants (DOACs) have recently joined warfarin for the treatment of atrial fibrillation, with a resultant significant expansion in use of oral anticoagulants (OACs). Our objectives are to compare safety and effectiveness of DOACs versus warfarin in a full population where anticoagulation management is good and to identify which types of patients do better with DOACs versus warfarin and vice versa.

**Methods and analysis:**

This is a retrospective cohort study of all adults living in British Columbia who have a diagnosis of atrial fibrillation in hospital or medical service data, and a first prescription for an OAC. Coprimary outcomes are ischaemic stroke and systemic embolism (benefit) and major bleeding (harm). Secondary outcomes include net clinical benefit (composite of stroke, systemic embolism, major bleeds, myocardial infarction, pulmonary embolism and death), drug discontinuation and individual composite item occurrence. We will estimate the effects of treatment in a 2-year follow-up period, using time-to-event models with propensity score adjustment to control confounding. Secondary analyses will examine ‘as treated’ outcomes.

**Ethics and dissemination:**

The protocol, data creation plan, privacy impact statement and data sharing agreements have been approved. Dissemination is planned via conferences and publications as well as directly to drug policy leaders. Information on the overall comparative effectiveness and safety of DOACs versus warfarin in a country with high quality anticoagulation management, as well as for vulnerable subgroups, will be an important addition to the literature.

Strength and limitations of this studyThis population-based retrospective cohort study minimises patient selection bias and prescribing channelling bias while examining comparative effectiveness and safety of oral anticoagulants.By linking patient-specific laboratory data, we hope to add additional essential information to determine predictors of outcomes.Although this is a large study of real-world patients, confounders, particularly unmeasured confounders, may create bias.The process of matching for purposes of comparative analysis leaves observational studies vulnerable to the loss of eligible patients.

## Introduction

Comparative effectiveness research (CER) priorities of the Institute of Medicine have highlighted the treatment of atrial fibrillation and the comparative effectiveness of anticoagulants as priority topics.^1^ This is because of the widespread use of oral anticoagulants (OAC), particularly in elderly populations, their major benefit in preventing morbid and fatal thrombotic events and their potential for major harm, which is largely bleeding. Large rigorous randomised trials have been critical to allowing direct acting oral anticoagulants (DOACs) on to the market, but have not settled whether their rapid uptake in clinical practice, probable use in patient groups beyond those included in the trials, and use in countries where international normalised ratio (INR) monitoring is relatively high quality generates similar benefits and harms compared to warfarin.^2–5^

Currently more than 7 million prescriptions are dispensed annually for OACs in Canada.^6^ Warfarin is one of the most cost-effective medications in current use, with a 68% reduction in stroke rates and a significant decrease in all-cause mortality in atrial fibrillation, at a negligible drug cost.^7^ Warfarin's narrow therapeutic index, the variability of its effect in some patients and concern regarding drug and food interactions mandate laboratory INR monitoring of its anticoagulant effect.^7^ The need for monitoring and dose adjustment is reassuring to some patients and is the ‘gold standard’ adherence check for drugs, but burdensome for other patients and for physicians. The DOACs are given in fixed doses and do not require (or benefit from) INR monitoring. Three of these, dabigatran, rivaroxaban and apixaban, are now available in Canada. Within a year of dabigatran launch in 2010, worldwide sales were estimated at US$1 billion annually.^8^ However, by 2011 the Institute for Safe Medication Practices (ISMP) and the Food and Drug Administration (FDA) noted that dabigatran was the leading cause of drug-related serious harm and death reported to the FDA in 2011.^9^
^10^

Several critical issues, outlined below, may significantly influence the relative effectiveness and safety of DOACs compared to warfarin in real-world practice and potentially produce different results than the pivotal trials. Patient characteristics, several of which have not previously been available to study, may predict a better benefit:harm ratio with warfarin versus DOACs or vice versa. Analyses of these features will improve the appropriate tailoring of anticoagulant therapy to individual patients.

The absolute (as opposed to relative) differences between DOACs and warfarin are quite small with 95% CIs ranging from 2 more to 8 fewer events per 1000 patients for stroke or systemic embolism, and 11 fewer to 6 more per 1000 for major bleeding.^11^ Consequently, there are several reasons why the advantages of DOACs might not be realised in usual clinical practice:
DOACs, especially dabigatran, are contraindicated in patients with severe renal impairment because of accumulating drug concentrations.^12^ Atrial fibrillation is primarily a disease of the elderly, older patients are vulnerable to rapid decline in renal function, and patients with renal impairment are at significantly higher risk of bleeding even without anticoagulation.DOACs have no marker (as the INR is for warfarin) for their effectiveness, safety or adherence. In addition, DOACs may produce more adverse symptoms (eg, dabigatran and gastrointestinal symptoms) than warfarin leading to undetected no-adherence. Finally, all DOACs have relatively short half-lives, and missed doses may have more impact on anticoagulation outcomes. While patient adherence is closely monitored in phase III clinical trials, monitoring in usual care is much more variable.Although antidotes are becoming available, their absence left no reliable way to stop DOAC-associated bleeding, and the antidotes will be very expensive and restricted to hospital settings.^13^ Patient monitoring and follow-up is less vigilant in clinical practice compared to clinical trials, thus the outcomes of bleeding may not be as favourable in usual practice.There are several DOACs available, each with separate dosages and dosing schedules depending on patient age and risk factors. Doses for atrial fibrillation differ from those for other indications. This will create confusion for prescribers, the vast majority of whom do not specialise in this area, and may lead to errors. Similarly, information on switching anticoagulants, bridging with DOACs, follow-up intervals, DOAC drug interactions, etc, is sparse.Time in therapeutic range (TTR) for INR is a good surrogate for warfarin safety and effectiveness.^14^ Study centres including Canadian centres, which maintained good average TTRs, saw no significant advantage to DOACs in clinical outcomes.^15^ It is unclear whether routine clinical practice maintains a good average TTR.

In summary, although the relative benefit:harm ratio of the two comparators in usual clinical practice remains uncertain, the importance of the outcomes is universal and unequivocal. Stroke, systemic arterial emboli and pulmonary emboli are frequently devastating and can be fatal, and major bleeding carries a death rate of 10% overall, 40% if intracranial.^16^ Cost-effectiveness and budget impact are also ongoing issues, as DOACs are much more expensive than warfarin. With the major clinical concerns in mind plus the rapidly increasing use of DOACs, there is an urgent and unmet need to evaluate outcomes in real clinical practice.

Observational studies using population-based health databases are increasingly used for CER because they can rapidly analyse large sample sizes with relevant outcome data across multiple comparators, entirely based in actual clinical practice and without any ethical concern about deliberate exposure to harm.^2^
^17^ Their main disadvantage relates to bias associated with non-random allocation, a bias now reduced with innovation in methods of case selection, follow-up, analysis and adjustment.^18–20^ Another essential component of comparative effectiveness and safety is the determination of the patient characteristics that predict a superior benefit:harm profile with one drug versus the other.

The linked healthcare databases of British Columbia (BC), Canada, are unusual internationally, as they include the entire population (∼4.7 million people). These databases include medications dispensed at community pharmacies (excluding the 4% who are federally insured), hospitalisations, medical services and vital statistics for BC residents.^21^ In addition, this study will incorporate a novel patient-level laboratory link for those laboratory results that are required to explain the comparative effectiveness and safety of anticoagulants. Previous studies comparing DOACs individually or as a group versus warfarin have either suffered from a lack of population-level data coverage (producing biased results) or examine only one outcome (not comprehensive).^22–27^

Our primary objectives for this study are as follows: (1) to clarify the overall comparative effectiveness and safety of DOACs versus warfarin in clinical practice where high quality is expected, (2) to compare and contrast our results with the relevant phase III randomised trials and (3) to identify the key predictors of superior effectiveness and safety (which drug is better for which patients) in vulnerable populations—predictors which are very likely to include INR control quality in the warfarin patients, remote location (probable lack of ready access to INR testing), access to certain specialists and presence of severe renal impairment.

## Methods and analysis

### Study design

The study will use a retrospective cohort design in which the treatment effects of new use of DOACs compared to warfarin are estimated, adjusted by propensity scores, for residents with a diagnosis of atrial fibrillation. This will allow us to preserve the population-based longitudinal data collection advantages, minimise selection and confounding biases and provide outcome data amenable to rapid clinical interpretation (eg, time to event analysis, relative risks, absolute risks, numbers needed to treat (NNT)).

### Study cohort

The source population includes all BC residents aged 18 years or older, an estimated 3.6 million individuals. Our access to BC data includes de-identified data extracts from PharmaNet, Medical Services Plan billings (physician payments), the hospital Discharge Abstract Database (DAD), BC Vital Statistics death records and LifeLabs laboratory data. All data are accessed once appropriate approvals and payment are received, using Population Data BC secure research servers.^21^ Our sampling frame will be BC residents enrolled with the Medical Services Plan during the 12 months before starting an anticoagulant drug (index prescription). Eligibility for inclusion in the cohort will be those with a diagnosis of atrial fibrillation in hospital or medical services data within the 36 months prior to the index prescription.

Anticoagulant exposure will be determined from dispensed prescription database records, beginning 1 October 2010 and continuing until study end (details in figure 1). New users of warfarin, dabigatran, rivaroxaban and apixaban will be identified. To identify new users, a look-back observation period of 12 months prior to the index prescription date will be used and must indicate no anticoagulant use during this period. The index date will be defined as date of the new prescription for OAC. Determination of exposure, as far as possible, will be blinded to patient outcome.

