### Analysis plan

The primary analysis will be intention-to-treat, meaning that if the index prescription is for warfarin, then any outcome events are attributed to warfarin whether switching occurs or not. This mimics the conservative, recommended analysis in clinical trials. However, this approach may underestimate benefit and harm, therefore a secondary ‘as-treated’ analysis will explore outcomes based on actual treatment during follow-up. Although both analyses occur after baseline confounders are adjusted for, the as-treated analysis requires further adjustments for measured time-varying confounding and selection bias using inverse-probability weighting.^34^ Switching between anticoagulants will be further explored by examining comparative duration on each anticoagulant as well as switch frequency.

For the main analysis, the effects of treatment with the use of DOACs versus warfarin will be estimated from time-to-event models (Cox proportional hazards or Poisson). Risk modifying effects such as age, sex, dose and risk factors (including congestive heart failure, hypertension, diabetes, prior stroke, prior major bleed, renal or liver failure, interacting concomitant medications, alcohol abuse) will be evaluated using tests of interaction. Tests of interaction will be used to identify key subgroups in which warfarin may be better than DOACs or DOACs better than warfarin, using the two coprimary outcomes and net clinical benefit as defined above. Models can simultaneously control for potential confounders such as cardiovascular disease, rural/remote location of residence, physician practice—all estimated at index date (further details in online supplementary appendix 1). Sample size is unlikely to allow individual DOAC versus DOAC comparison, but outcomes will be tabulated by individual drug.

Community-based outcome event rates and the RE-LY trial suggest a coprimary outcome event rate of ∼12% per year for warfarin versus 10% per year for DOACs.^3^
^35^ Assuming conservatively that accrual extends over 3 years and that patients have a minimum of 1 year of follow-up, and that 67% of the sample is on warfarin, an analysis based on outcomes at 1 year would require 6000 patients on warfarin and 3000 patients on DOACs for 80% power. Since our analysis will be time-to-event rather than using binary outcomes at 1 year, we expect to have greater power than estimated.

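### The cohort rule does not tie the index prescription to atrial fibrillation, and the named propensity variables omit valve disease, venous thromboembolism and recent surgery

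*Protocol article*

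**What the plan says.** The Study cohort section of the protocol article gives the entry rule: "Eligibility for inclusion in the cohort will be those with a diagnosis of atrial fibrillation in hospital or medical services data". The look-back for that diagnosis is three years from the first dispensing. Exposure is equally broad: "New users of warfarin, dabigatran, rivaroxaban and apixaban will be identified" from dispensing records. The only negative criterion is the 12-month look-back, which "must indicate no anticoagulant use during this period". The abstract defines the cohort in the same way, as adults "who have a diagnosis of atrial fibrillation in hospital or medical service data, and a first prescription for an OAC".

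Follow-up runs to a maximum of 24 months and is cut short by death, leaving the province or the end of the study window (Follow-up). The primary analysis is by index drug: for a warfarin index prescription, "any outcome events are attributed to warfarin whether switching occurs or not" (Analysis plan).

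Control for confounding lists the variables considered for the propensity score. They include dose, two risk scores, concomitant medications, physician specialty and a general item for other vascular events. Valve disease, VTE and recent surgery are not named. A high-dimensional score with empirically chosen variables is also to be evaluated.

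The Introduction acknowledges that these drugs have other uses: "Doses for atrial fibrillation differ from those for other indications".

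**The concern.** An AF code up to three years old plus any new anticoagulant does not show that the drug was started for AF. A patient with an old AF code who is anticoagulated for a valve, a clot or an operation meets the rule as written.

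Four parts of the plan would be affected:

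- **Primary contrast.** If other indications are distributed unequally between drugs, the contrast mixes the effect of the drug with the effect of the indication.
- **Discontinuation.** A therapy gap of more than 30 days counts as stopping, so a completed short course for another reason would be scored as abandoned AF treatment.
- **Net clinical benefit.** The composite includes pulmonary embolism, and patients treated for recent VTE would be expected to bring that risk with them.
- **Second objective.** Comparison with the phase III trials is harder to interpret if part of the cohort is not being treated for AF.

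**Working it through.** **1. Is the gap in the stated rule, or only in what is not shown?** The rule appears twice, in the abstract and under Study cohort, and neither statement contains an indication criterion. The appendix is cited for data codes (Data codes) and for further detail on confounders (Analysis plan). Figure 1 is captioned as time frame definitions. Neither is described as setting eligibility.

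**2. The plan's own sample size.** Inputs from the Analysis plan: 12% v 10%, two warfarin patients per DOAC patient, 80% power, two-sided 5%. The pooled proportion is (2 × 0.12 + 0.10)/3 = 0.1133.

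n(warfarin) = [1.960 × √(0.1133 × 0.8867 × 3) + 0.842 × √(0.12 × 0.88 + 2 × 0.10 × 0.90)]² / 0.02² = 5,822, with 2,911 on DOACs.

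With continuity correction the figures are 5,971 and 2,986. The stated 6,000 and 3,000 reproduce, and give 81.2% power without the correction. The planned contrast is a risk ratio of 0.10/0.12 = 0.833.

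**3. Illustration of what contamination could do.** The documents give no share of patients with another indication and no risk for them, so both inputs are assumptions. Suppose the drugs are equivalent (10% risk in both arms), a share f of the warfarin arm has m times that risk, the DOAC arm has no such patients, and nothing is adjusted. Then:

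- warfarin risk = 10% × [1 + f(m − 1)]
- SE = √[p_w(1 − p_w)/6000 + 0.10 × 0.90/3000]

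| f | m | Warfarin risk | DOAC:warfarin risk ratio | Chance of p<0.05 |
|---|---|---|---|---|
| 5% | 1.5 | 10.25% | 0.976 | 6.6% |
| 5% | 2 | 10.5% | 0.952 | 11.5% |
| 10% | 2 | 11.0% | 0.909 | 31.2% |
| 20% | 2 | 12.0% | 0.833 | 82.6% |
| 10% | 0.5 | 9.5% | 1.053 | 11.7% |
| 20% | 0.5 | 9.0% | 1.111 | 32.8% |

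At 5-10% and double risk, the spurious difference is 0.5 to 1.0 percentage points, a quarter to a half of the planned 2 points. With m below 1 the sign reverses.

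**4. What restriction costs in power.** From 81.2% at 6,000 and 3,000:

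- removing 5% or 10% of the warfarin arm only leaves 80.5% or 79.8%
- removing 5% or 10% of both arms leaves 79.2% or 76.9%

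**The case against.** **Silence in a condensed article.** The paper condenses a fuller protocol, and exclusion codes could sit in an appendix that is not shown. That possibility stands, and no sentence says that other indications are deliberately kept. But eligibility is a core element stated twice without such a limit, so the plan followed as written admits these patients.

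**Planned adjustment.** The high-dimensional score draws on medication, hospital and billing data, where valve, clot and surgery codes would sit. Cardiovascular disease is also mentioned as a model covariate. The article's limitations refer to matching, which would tend to drop patients with almost no chance of a DOAC, provided the score contains the relevant diagnosis. The as-treated analysis and marginal structural models deal in part with short courses. All this is real protection for VTE and surgery, where both drug types may be used. A reader might infer that no propensity score can handle any of these patients, but that holds only for an indication with no realistic choice of comparator.

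**Direction.** A reader might also infer that the result is biased against warfarin. The documents do not support that: it requires an assumed higher risk in the added patients, and the illustration reverses when their risk is lower.

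**Deliberate breadth.** The aim is a full-population study of "all adults living in British Columbia who have a diagnosis of atrial fibrillation" and a first anticoagulant, and the Introduction treats use beyond the trial populations as an open question. A patient with AF and a recent clot still has AF. This objection stands against removing every such patient from the primary cohort.

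**The dosing sentence.** The Introduction's remark on doses concerns prescriber confusion. It shows awareness of other indications and nothing about cohort definition.

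**Conclusion.** The concern holds in a limited form. The entry rule does not link the index prescription to AF, the named confounders omit the main competing indications, and up to 24 months of events (a maximum, not a fixed period) are attributed to the index drug.

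- For an indication treated in practice with one comparator only, there is no overlap and adjustment cannot repair the contrast. That mechanical valve is such an indication is an assumption that the document does not state.
- For VTE and recent surgery, the problem is confounding and dilution, which the high-dimensional score and the as-treated analysis reduce but do not remove.

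The document fixes neither the size nor the direction of bias. The increase of 5-10% in the warfarin rate rests on an assumed 5-10% share at double risk, confined to the warfarin arm and unadjusted. The 12% v 10% figure is described only as a coprimary outcome rate, so it is a yardstick and not a bleeding or stroke rate. A demonstrated bias cannot be claimed, but the exposure to bias is avoidable and should be closed.

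**What to change.** 1. In the primary cohort, exclude patients in both arms who have pre-index codes for mechanical valve or mitral stenosis.
2. Name VTE and orthopaedic surgery shortly before the index date as propensity covariates, with the look-back window fixed in advance. Add a sensitivity analysis that excludes these patients.
3. Report the unrestricted cohort as a further sensitivity analysis, so that the full-population result remains available.
4. If the appendix already applies such exclusions, state them in the Study cohort section.

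The hospital and billing data are already part of the planned linkage, so the work is extra code lists and two further runs. The cost is a slightly smaller primary cohort that is less fully all-comers, with the modest loss of power shown above if the shares excluded are of that order.

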**Figure 1 BMJOPEN2016013263F1:**
[figure not shown]
Time frame definitions.

### Outcomes

The coprimary outcomes, chosen for their clinical importance and their similarity to those in the pivotal trials, will be ischaemic stroke and systemic embolism, and major bleeding defined as bleeding requiring hospitalisation. Intracranial haemorrhage (ICH) will be counted as part of major bleeding. Secondary outcomes include: (1) net clinical benefit, defined as a composite of ischaemic stroke, systemic embolism, major bleeds, myocardial infarction, pulmonary embolism and death. This composite was used in RE-LY and is a good summary representation of clinically important benefit and harm. All of these outcomes will be identified in hospital DAD, or vital statistics data, and have been validated;^28–32^ (2) discontinuation using dispensing gap analysis. Discontinuation is defined as a calculated gap of more than 30 days in therapy and (3) the individual clinical outcomes that are part of net clinical benefit composite plus components of major bleeding (notably ICH and gastrointestinal bleeding). By incorporating all relevant serious events into the net clinical benefit, we avoid the problem of competing risks.^33^

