### Follow-up

Outcomes will be counted in a follow-up window to 24 months postindex prescription, death, exit from BC or the end of the study window. We will censor follow-up for death or departure from the province, but not clinical outcomes, in order to gather information on the clustering of important clinical events (eg, patient has a bleed, discontinues warfarin, then has a vascular event and dies).

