Missing data, including missing laboratory results, are represented as variables in the propensity score. All analyses will be carried out using SAS. 95% CIs for the estimates will be calculated, with two-tailed, p<0.05 considered significant. Absolute risk difference and NNT to benefit or harm will be calculated. Analysis and reporting will be compliant with Strengthening the Reporting of Observational Studies in Epidemiology (STROBE) recommendations.^36^

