### Control for confounding

New users of DOACs are likely to differ in several characteristics from new users of warfarin. We expect them to be younger and with less comorbidity. To control for confounding, we will adjust estimates by age, sex and propensity score. Propensity scores will be computed by multiple logistic regression of the logit of the conditional probability of allocation to warfarin versus any DOAC (conditional on patient being a new user of either anticoagulant) regressed on potential confounders at baseline. Among the variables considered will be sex, dose, CHADS_2_ (Congestive heart failure, hypertension, age, diabetes, stroke - 2 points) score, and HAS-BLED score (hypertension, abnormal renal or hepatic function, previous stroke, bleeding, labile INR, age, drugs/alcohol), other vascular events, concomitant medications, drug plan coverage, remote location, neighbourhood income quintile, physician specialty, haemoglobin and year of cohort entry. We plan to evaluate conventional and high-dimensional propensity scores, the latter estimated using preselected and empirically chosen variables from medication, hospital and medical services data.^37^

Analyses of switching patterns, including the duration of OAC exposure and the switching frequency, will be treated as time-dependent confounders and controlled by marginal structural modelling.^38^

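### The statement that competing risks are avoided holds only for the secondary composite; death still competes with both coprimary outcomes, and their absolute risks and NNTs need an estimator that allows for it

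*Protocol article*

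**What the plan says.** Four statements in the protocol article bear on this.

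- **Outcomes, coprimary.** They "will be ischaemic stroke and systemic embolism, and major bleeding defined as bleeding requiring hospitalisation". All-cause death is in neither.
- **Outcomes, secondary.** The first is "net clinical benefit, defined as a composite of ischaemic stroke, systemic embolism, major bleeds, myocardial infarction, pulmonary embolism and death". The individual members of that composite are listed as further secondary outcomes, so death is also an outcome in its own right. The section then concludes: "By incorporating all relevant serious events into the net clinical benefit, we avoid the problem of competing risks".
- **Follow-up.** "We will censor follow-up for death or departure from the province, but not clinical outcomes". The observation window is at most 24 months.
- **Analysis plan.** Effects come from Cox or Poisson models. In addition, "Absolute risk difference and NNT to benefit or harm will be calculated". The article does not say how the absolute risks will be obtained.

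The article has no other provision for competing risks.

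**The concern.** A composite that counts death cannot be pre-empted by death, so for net clinical benefit the assurance is correct. It does not carry over to outcomes that leave death out. A patient who dies of another cause can no longer have a stroke, an embolism or a bleed, so death competes with both coprimary outcomes and with every non-fatal component. The sentence is unqualified and ends the paragraph that defines all the outcomes, so a reader or analyst could take it to mean that nothing further is needed.

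Relative effects are not the problem. What is at stake is the absolute scale. A risk read from a survival curve censored at death describes a population in which nobody dies of anything else, and it exceeds the proportion of patients who will actually have the event. The Introduction describes atrial fibrillation as mainly a disease of older people and calls the absolute differences between the drug classes quite small, a matter of a few events per 1000. Results are meant for drug plan managers, who will use risk differences and NNTs directly. An avoidable inflation matters more in that setting.

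**Working it through.** **The plan's own figures.** The article gives no figure for competing risks and no death rate. Its sample size (6000 warfarin and 3000 DOAC patients for 12% v 10% at one year, 80% power, two-sided 0.05) reproduces: 5822 and 2911 without continuity correction, 5971 and 2986 with it. It does not bear on this point.

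**Inputs.** From the article: a 24-month window, so T = 2 years; censoring at death; and 12% v 10% per year as coprimary event rates, used below as hazards. Assumed, because the article does not give them: all death rates, and the lower event rates used for stroke alone and bleeding alone.

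**Formulas**, with constant yearly hazards h (event) and d (death without the event):

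- Death-censored risk: 1 − exp(−hT)
- Cumulative incidence with death competing: h/(h + d) × [1 − exp(−(h + d)T)]

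**Equal mortality in both arms**

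| Event rate per year, warfarin v DOAC | Death per year, both arms | Death-censored difference per 1000 (NNT) | Cumulative incidence difference per 1000 (NNT) | Overstatement |
|---|---|---|---|---|
| 3.0% v 2.7% | 5% | 5.67 (176) | 5.40 (185) | 5% |
| 2.0% v 1.7% | 8% | 5.78 (173) | 5.35 (187) | 8% |
| 12% v 10% | 5% | 32.1 (31) | 30.7 (33) | 5% |
| 12% v 10% | 10% | 32.1 (31) | 29.3 (34) | 9% |

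The second row in full, warfarin then DOAC:

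- Death-censored: 1 − exp(−0.040) = 3.92% and 1 − exp(−0.034) = 3.34%.
- Cumulative incidence: 0.020/0.100 × [1 − exp(−0.200)] = 3.63% and 0.017/0.097 × [1 − exp(−0.194)] = 3.09%.
- Ratio of the unrounded differences: 5.78/5.35 = 1.08.

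Over a wider assumed range of equal mortality, 3% to 15% per year, each arm's risk is overstated by about 3% to 15%.

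**Mortality still unequal after adjustment**

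| Event rate per year, warfarin v DOAC | Death per year, warfarin v DOAC | Death-censored difference per 1000 (NNT) | Cumulative incidence difference per 1000 (NNT) |
|---|---|---|---|
| 2.0% v 1.7% | 10% v 8% | 5.78 (173) | 4.66 (215) |
| 4.0% v 3.6% | 10% v 6% | 7.41 (135) | 4.27 (234) |
| 12% v 10% | 10% v 6% | 32.1 (31) | 23.0 (43.5) |

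The size and direction depend on which arm has the higher mortality. Reversing the first row (8% warfarin, 10% DOAC) gives cumulative incidences of 3.63% and 3.03%, a difference of 5.94 per 1000, so the death-censored 5.78 would then be slightly too small.

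**The case against.** The strongest reply is that the article never says absolute risks will come from death-censored curves. It promises risk differences and NNTs and stops there. Rate differences per unit of person-time, or cumulative incidence, would not carry this bias, and a condensed article may leave the estimator to a fuller document. This stands. A reader might infer that the absolute risks and NNTs will certainly be wrong; the article does not support that.

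A reader might also infer that censoring at death invalidates the main comparison. It does not. It is the standard basis for a cause-specific hazard or rate ratio.

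On mortality, the article says of DOAC users: "We expect them to be younger and with less comorbidity". It would be tempting to conclude that the unequal-mortality figures apply. But that sentence describes unadjusted baseline differences, and adjustment for age, sex and propensity score follows immediately. Unequal mortality would matter only as far as it survives adjustment, through residual confounding or a drug effect on death. Even then, part of the change reflects the choice of estimand: patients who live longer have more time to have an event, and both quantities can be interpreted.

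Finally, death is already an individual secondary outcome, so reporting it separately adds nothing new to the plan.

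None of this rescues the sentence in Outcomes. It is a statement in the text, not an omitted detail, and as an unqualified claim it is wrong for the coprimary outcomes.

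**Conclusion.** The point holds in limited form, at moderate severity. The assurance on competing risks is correct for net clinical benefit and incorrect for both coprimary outcomes and the non-fatal components, for which death is a competing event handled by censoring. The Cox or Poisson ratios stand as cause-specific measures. Risk differences and NNTs would be overstated only if derived from the death-censored time-to-event analysis, which the article neither states nor rules out.

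The likely size is modest: about 5% to 8% of the 24-month risk difference under equal mortality of 5% to 8% per year. It becomes substantial (NNT 173 v 215 in the stroke example) only if mortality is still clearly lower on DOACs after adjustment. All these sizes rest on constant hazards and on assumed death rates.

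**What to change.** 1. In Outcomes, restrict the sentence on competing risks to net clinical benefit.
2. Label the hazard or rate ratios for the coprimary and non-fatal component outcomes as cause-specific.
3. State that 24-month absolute risks, risk differences and NNTs to benefit or harm for these outcomes come from Aalen-Johansen cumulative incidence, propensity-weighted or standardised, with death without the event as the competing event.
4. Report the already planned death outcome next to them, so that readers can see whether mortality differs between arms.

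The cost is a few lines of text and a little more analysis. Vital statistics death records are already among the linked sources, so no new data are needed. The reported absolute risks will be slightly smaller.
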